### Assignment of interventions: blinding

#### Who will be blinded {17a}

Participants, mental health first aiders and researchers will not be blinded to treatment allocation due to the nature of the study. However, independent staff helping to process the data, the trial statistician and health economist will all be blinded to intervention status.

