### Outcomes {12}

#### Primary outcome

The primary outcome is Employees’ help-seeking behaviour at 6 months measured by the Actual Help-Seeking Questionnaire [AHSQ] [11]. The AHSQ measures help-seeking behaviour in the 2 weeks preceding the assessment and will be assessed at baseline, 6, 12 and 24 months. Help-seeking behaviour is determined by listing the number of help sources, the type of help sought and whether help seeking has occurred during the allocated time period.

The primary analysis will be conducted on those participants who receive MHFA and therefore is a per protocol analysis. Further analyses will examine the impact of the intervention at the organisational level using an intention-to-treat analysis with all respondents included.

As this is a small non-random subsample of randomised participants, it is recognised that this analysis will be vulnerable to selection bias and uncontrolled confounding. For this reason, a range of baseline participant characteristics will be included in the primary analysis to mitigate these limitations.

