#### Secondary outcomes

All secondary outcomes and their measures are described in Table 1. In addition to these outcome measures, the researchers will also capture data on organisations’ sickness absence levels, presenteeism rates and measures of productivity.

**Table 1 Tab1:** Data collection schedule and secondary outcome measures

Measure	Timing of measures				
	Baseline	Post-intervention (up to 3 months)	6 months	12 months	24 months
Demographics (age, gender, level of education, ethnicity, nature and frequency of and MHFA interventions directly experienced, etc.)	X				
Employees help-seeking intentions (General Help-Seeking Questionnaire) [12]	X	X	X	X	X
Employees’ mental health and wellbeing (Warwick-Edinburgh Mental health and Well-being Scale) [13]	X	X	X	X	X
Mental health first aiders’ mental health literacy (Mental Health Literacy Scale) [14]^a^	X	X	X	X	X
Mental health first aiders’ skills (ALGEE scoring system) [15]^a^	X	X	X	X	X
Employees’ quality of life (EQ-5D-5L and Short Form-12 Health Survey SF-12) [16]	X	X	X	X	X
Employees’ self-efficacy (Self-Efficacy for Seeking Mental Health Care Scale) [17, 18]	X	X	X	X	X
Employees’ social well-being (Social Well-being Scale) [19]	X	X	X	X	X
Employees’ use of standard mental health and other services (adapted version of the Client Services receipt Inventory) [20]	X	X	X	X	X

^a^Intervention group

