### Assessment of cost-effectiveness

This component will answer the research question ‘Is MHFA more cost-effective than usual practice?’ This requires comprehensive estimates of the financial benefits derived from MHFA and its costs. Consequently, the evaluation will analyse the data from three perspectives reflecting the three main groups impacted by MHFA:
Personal (employees’ quality of life)State/government (use of health and social services)Employers (staff productivity)

Data will be combined with unit cost data to provide a financial estimate of the change in service use observed. The results for those who had the MHFA training and those who did not will determine whether it is more cost-effective to purchase the training or not.

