### Methods for additional analyses (e.g. subgroup analyses) {20b}

Age, gender, level of education, ethnicity, nature and frequency of MHFA interventions directly experienced will be included in the primary analysis as covariates.

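### The data staff, statistician and health economist cannot stay blinded throughout: one-arm scales, a receipt-defined primary analysis and a trained-versus-untrained cost comparison can reveal an organisation's arm

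*Protocol article*

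**What the plan says.** The protocol article, Who will be blinded {17a}, declares participants, first aiders and researchers open, and then says that "the trial statistician and health economist will all be blinded to intervention status", in a sentence that also covers the independent staff who process the data. It sets no limit by stage, dataset or analysis, and the section on unblinding is marked as not applicable.

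Other sections describe the data and analyses that these people will handle:

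- **Secondary outcomes, Table 1.** First aiders' mental health literacy and ALGEE skills scores are scheduled at all five time points. Both carry a footnote, which reads "a^Intervention group".
- **Primary outcome.** "The primary analysis will be conducted on those participants who receive MHFA", which the article calls a per protocol analysis. An intention-to-treat analysis of all respondents is a further analysis.
- **Assessment of cost-effectiveness.** "The results for those who had the MHFA training and those who did not" are to settle whether buying the training is worthwhile.
- **Randomisation.** The organisation is the unit, and allocation follows completion of baseline measures.
- **Explanation for the choice of comparators {6b} and Relevant concomitant care {11d}.** Control organisations agree not to take up the training while the study runs.

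**The concern.** In a cluster trial, a field that is filled in one arm only identifies more than the person who filled it. It identifies the organisation, and so every colleague in it. If such fields sit in the analysis dataset, calling the arms A and B hides nothing.

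What is at stake is analytic discretion. The Primary outcome section concedes that the recipient analysis is a small, non-random subset open to selection bias and confounding. The article leaves open who counts as a recipient, which control employees they are compared with, which further baseline covariates enter, and which missing-not-at-random scenarios are run. These are the choices for which a reader would want assurance that the analyst did not know the arm. A trial report that repeated the present blinding statement would give that assurance for analyses that cannot have it.

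**Working it through.** The plan gives no figure to reproduce on this point, so the check is mainly to set the sections side by side.

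**1. Intervention-only scales.** Table 1 confines the literacy and ALGEE scores to the intervention group. Because allocation follows baseline, I do not rely on the baseline column; four later time points remain. A filled value at any of them marks the employer as an intervention organisation. Employer is also a random effect in the primary model (Statistical methods {20a}), so the analyst must hold the organisation identifier. One record therefore gives the arm of all employees in that cluster. If arms carry a two-letter code, one identified organisation decodes the label for all 24.

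**2. Receipt-defined primary set.** The analyst must select on receipt of MHFA. Control organisations should have no MHFA training under the trial, so a positive receipt flag points to the intervention arm. It is not perfect proof: the exclusion criterion bars only organisations that had introduced MHFA across all sites and departments, so some earlier contact among control employees is not clearly ruled out.

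**3. Economic comparison.** Trained and untrained staff cannot be contrasted, nor training cost charged to one side, without knowing who was trained.

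**4. The exposure covariate.** Under Methods for additional analyses {20b}, "nature and frequency of MHFA interventions directly experienced will be included in the primary analysis as covariates". Table 1 lists this item under demographics, at baseline only, which is before allocation. As scheduled it does not reveal the arm, so I do not count it.

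**5. How likely is a revealing record? (illustration only)** Inputs: an average of 72 employees per organisation, a 40% response rate and 12 intervention organisations (Sample size {14}); one first aider recommended per ten staff (Intervention description {11a}). Assumptions: organisations follow the recommendation, and first aiders respond independently at the overall rate.

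- First aiders in an average organisation: 0.10 × 72 = 7.2, about 7.
- Expected responders among them: 7 × 0.40 = 2.8.
- Chance of at least one scored first aider at a given time point: 1 − 0.6^7 = 1 − 0.028 = 0.97.
- With only two first aiders, as a small organisation might have: 1 − 0.6^2 = 0.64.
- Expected number of intervention organisations identified at one time point by this route alone: between 12 × 0.64 = 7.7 and 12 × 0.97 = 11.6.
- Chance that at least one intervention organisation is identified, which is enough to break a coded label, even with a single first aider in each: 1 − 0.6^12 = 1 − 0.002 = 0.998.

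Receipt flags and training records add further routes.

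**The case against.** The best reply is that a condensed article says who is blinded and leaves the method to a data management plan or SAP that is not shown. Coded arms, withheld variables or staged release may well be planned. That is fair, and their absence from the article is not the point. The point is that no such procedure can keep the analyst blinded while running a recipient analysis, scoring intervention-only scales or costing the training.

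A reader might infer several stronger things that the documents do not support:

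- **That analyst blinding is wholly illusory.** It is not. With the revealing fields withheld, cleaning and the all-respondent analysis can be done masked.
- **That the exposure covariate in the primary model reveals the arm.** It is scheduled before allocation, so as written it does not.
- **That all 12 intervention organisations are identifiable on opening the data.** Organisations may train any number of staff and response is partial. The illustration gives most of them, and the documents do not show all.
- **That the health economist must know the arm from the start.** Service use, quality of life and productivity could be analysed by coded group, with training status and cost attached last.
- **That this is the trial's one safeguard against bias.** Allocation after baseline is another. Analyst blinding also could not protect the primary outcome's measurement, because unblinded employees report it themselves.

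It is also true that much of the problem follows from defining the primary analysis by receipt. The one-arm scales and the economic comparison would remain if that changed.

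**Conclusion.** The blinding statement is broader than the plan can deliver. It fails for the recipient analysis, which is the stated primary one, for the intervention-only outcomes, and for the economic comparison once training status and cost are attached. It also fails for any data-processing staff who see those fields. It can hold for data cleaning and the all-respondent analysis, provided the revealing fields are kept back.

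This is a contradiction between sections, not a numerical error. No sample size, error rate or estimate changes, and the protection at issue covers analytic decisions only. The conclusion rests on the table footnote meaning that the scales are collected in the intervention group alone, and on control organisations keeping to their undertaking. It does not depend on the response-rate illustration. It should be put right before analysis.

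**What to change.** 1. **First release.** The research team, which is already unblinded and already exports the data (Data management {19}), supplies a dataset with coded arms and without the intervention-only scales, MHFA-receipt fields and training records. The all-respondent 6-month model and its result are locked on this dataset.
2. **Before any receipt data are released.** Fix in writing the definition of a recipient, the comparison group, the covariates, the missing-not-at-random scenarios and the code for the recipient analysis. Without this step the stated primary analysis would gain nothing from the masking.
3. **Second release.** Receipt, first-aider and training-cost data follow the lock.
4. **Restate the blinding section.** The statistician is blinded only up to the lock. The recipient and intervention-only analyses are run unblinded. The health economist is not blinded once training status and cost are attached. Staff who handle the withheld fields are not described as blinded.

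The stripping of fields should not go to the data-processing staff while they are described as blinded, since they would have to see what they remove.

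The change needs no new data and leaves design and sample size as they are. It costs a short delay to the receipt-based and economic analyses, and a less favourable blinding statement in the report.

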#### Procedure for unblinding if needed {17b}

N/A due to the nature of the trial.

### Data collection and management

#### Plans for assessment and collection of outcomes {18a}

Consent, baseline and follow-up data will be collected online, with the option for employees to complete them in hard copy should they be unable to complete them online. The research team will email the designated contact from each organisation, giving instructions and information for them to send to ALL employees and a link to the survey. One, 2 and 3 weeks later, follow-up emails will be sent to the same contact, asking them to send a reminder email, with a repeat survey link. After this period, participants who have not completed the survey will be treated as lost to follow-up.

#### Plans to promote participant retention and complete follow-up {18b}

Participants will be sent up to four weekly reminders to complete the survey at each time point.

### Data management {19}

Participant data will be exported from Qualtrics into SPSS version 22 by the research team (and any hard copies entered manually), stored on a password-protected network drive, will be accessible only to research team members and will only be linked directly with their participant ID code.

### Confidentiality {27}

Stored data will only be linked directly with the participant ID code. Any hard copies of data will be destroyed by confidential waste disposal 15 years after the research findings have been published. Electronic copies of data will be stored in two archives. In both cases, only anonymous data will be archived at London South Bank University archive and a national data repository.

### Plans for collection, laboratory evaluation and storage of biological specimens for genetic or molecular analysis in this trial/future use {33}

N/A as no biological specimens were collected as part of this trial.

### Statistical methods

#### Statistical methods for primary and secondary outcomes {20a}

All outcomes will be described with the appropriate descriptive statistics: mean and standard deviation for continuous outcomes (or medians and interquartile range for skewed data) and counts and percentages for dichotomous and categorical outcomes.

The analysis of the primary outcome will estimate the mean difference (with 95% confidence intervals) in the Actual Help-Seeking score at 6-month follow-up between the intervention (MHFA) and standard care groups using a mixed effects repeated measures model (which assumes incomplete outcome data to be missing at random). The model will incorporate demographic and other baseline covariates as fixed effects. The dependent variable will be the count of help sources on the Actual Help-Seeking questionnaire. The independent variable will be ‘time point’. The effect size of the intervention will be estimated as the exponentiated coefficient for the interaction term between time point (baseline versus 6-month follow-up) and intervention status (MHFA versus control group). A random effect of participant will be included in the model to adjust for the repeated measures on participants. ‘Employing organisation’ will be included as a higher level random effect (with participants nested in employers). Statistical significance will be at the 5% level.

Secondary outcomes will be analysed using an appropriate generalised linear model, for example binary logistic regression for dichotomous outcomes and ordinal logistic regression for ordered categorical outcomes. All models will be adjusted for employing organisation and baseline score (where applicable).

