**Fig. 1 Fig1:**
[figure not shown]
CONSORT trial flow diagram

To be able to detect a change of two additional help seeking resources [11], with 80% power at the 0.05 alpha level, assuming that the mean in the control group is 1 and in the intervention group 3 with a common standard deviation of 8, 506 participants are required, increasing to 596 allowing for 15% attrition at 6 months. Pilot data indicates a response rate of 40% across organisations and an average cluster size of 72 employees (calculated from organisations currently signed up) therefore approximately 29 employees per organisation (cluster size). With 24 clusters, 12 organisations per condition, and assuming an intraclass correlation coefficient (ICC) equal to 0.01 (ICC’s are lower for participant outcomes as opposed to process variables, when cluster size is large and when estimates are adjusted by participant baseline characteristics [21]), a minimum target sample size is 763, rounded up to 800, 400 per condition

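### In the primary model as written, baseline covariates cancel from the time-by-arm effect for participants measured twice, so they do not address confounding of change in the per-protocol analysis

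*Protocol article*

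**What the plan says.** Four places in the protocol article bear on this.

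- **Outcomes {12}** makes the primary analysis per protocol, restricted to people who receive MHFA. It accepts that they are not a random subset and that the comparison is exposed to selection and confounding. Its stated answer is to include baseline participant characteristics in the primary analysis.
- **Statistical methods {20a}** fixes the model: "The dependent variable will be the count of help sources on the Actual Help-Seeking questionnaire", and "The model will incorporate demographic and other baseline covariates as fixed effects". The effect is the "exponentiated coefficient for the interaction term between time point (baseline versus 6-month follow-up) and intervention status". On the repeated measurements it says: "A random effect of participant will be included in the model to adjust for the repeated measures on participants". Organisation is a further random effect. No covariate-by-time term is mentioned.
- **Methods for additional analyses {20b}** lists age, gender, education, ethnicity, and the kind and amount of MHFA personally experienced, and says these "will be included in the primary analysis as covariates".
- **Table 1** schedules all of these at baseline only, so each has a single value per person.

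**The concern.** The effect is a contrast of changes: movement from baseline to 6 months in the MHFA group, minus the same movement in controls. A covariate with one value per person, entered as a main effect, adds the same amount at both times and so cannot influence a change.

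The contrast already removes stable differences in level between recipients and controls. What it leaves is confounding of change: people who come to receive MHFA may be on a different course (for example, becoming unwell and about to seek help more widely). That is a plausible form of selection by receipt of MHFA, and it is what the covariates would have to address. If they do not, the primary result would be presented as adjusted while the one stated safeguard has done little.

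**Working it through.** **Inputs from the protocol.** Model, effect term and covariates as above; 24 organisations, about 29 respondents each; SD 8; difference 2; 15% attrition at 6 months.

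**1. Linear model, both times observed.** Let A be arm, t time (0 or 1), x the covariates, u the organisation effect and p the participant effect:

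y(t) = a + b·t + c·A + d·t·A + g·x + u + p + e(t)

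The within-person change is y(1) − y(0) = b + d·A + e(1) − e(0). The terms in x, u and p have gone. The person's total carries g·x, but its own free intercept and arm term mean that it says nothing further about d. The estimate of d is the difference in mean change, with or without x.

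**2. Poisson model with log link, both times observed.** Given a person's total count, the 6-month count is binomial with log-odds b + d·A. The factor exp(g·x + u + p) is common to both times and cancels. The distribution of the total has its own free intercept and arm term, so again d does not depend on x.

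**3. What remains.** Suppose change also depends on x with slope h. The estimate then tends to d + h × (mean x in recipients − mean x in controls). A main effect g does not estimate h; an x-by-time term does.

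**4. Illustration.** The following are assumptions, not protocol figures: true effect 2; x standard normal, with slope 3 on level and 2 on change; SDs of 0.8 (organisation), 5 (participant) and 5.5 (residual). The baseline SD is then √(9 + 0.64 + 25 + 30.25) = √64.89 = 8.06, close to the protocol's 8. The intention-to-treat set is 24 × 29 = 696 people. The per-protocol set keeps all 348 controls and, in the MHFA arm, people whose chance of receipt rises with x. That leaves on average 454 people, so about 106 recipients. Dropout depends on x, in opposite directions by arm. There were 12 simulated trials per row, each fitted with a three-level Gaussian mixed model. Entries are mean estimates.

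| Set and data | No covariate | Main effect | Main effect + covariate × time |
|---|---|---|---|
| Per protocol, complete | 3.34 | 3.34 | 2.21 |
| Per protocol, about 16% missing | 2.56 | 2.99 | 2.19 |
| Intention-to-treat, complete | 1.98 | 1.98 | 1.95 |
| Intention-to-treat, about 15% missing | 1.33 | 1.74 | 2.05 |

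With complete pairs, no simulated trial showed any difference between the first two columns (maximum 0.000000). The standard errors also matched: 0.884 and 0.884 per protocol, 0.605 and 0.605 intention-to-treat. Crossing with time removed 3.34 − 2.21 = 1.13 of the 1.34 excess. The remaining 0.21 is within simulation error, roughly 0.886/√12 = 0.26.

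A random-intercept Poisson model (10 simulated trials, 696 people) agreed. With complete pairs the interaction was 0.3886 with and without the covariate. With dropout it moved from 0.2815 to 0.3458 (rate ratio 1.33 to 1.41).

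**5. Sample size, as a side check.** A two-sided t-test for difference 2 and SD 8 needs 253 per arm, 506 in total. Then 506/0.85 = 595.3, so 596. The design effect is 1 + 28 × 0.01 = 1.28, and 596 × 1.28 = 762.9, so 763. The protocol's figures reproduce and this point does not alter them.

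**The case against.** **Wording.** Calling the covariates fixed effects may only distinguish them from random effects. It does not expressly rule out covariate-by-time terms, and an analysis plan that is not shown could add them. That is fair, but main effects are the natural reading. The protocol states a model and claims a benefit for it that the model does not give, so this is more than missing detail.

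**Missing data.** The model keeps incomplete cases ("which assumes incomplete outcome data to be missing at random"), and 15% attrition is expected. People seen once bring in between-person information, so the main effect does move the estimate. This stands. In the intention-to-treat illustration it reduced dropout bias (1.33 to 1.74, truth 2). In the per-protocol one it moved the estimate away from the truth (2.56 to 2.99). Movement through incomplete pairs is not control of confounding by receipt.

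**Choice of count model.** Exact cancellation is a linear and Poisson result, and the protocol names no distribution. In simulated overdispersed counts with complete pairs (assumed covariate coefficient 0.6, dispersion 0.8), a negative binomial interaction moved by 0.004 to 0.116 on the log scale. This limits the word exact, but does not show that confounding of change is removed.

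**Wider readings.** A reader might infer that adjustment changes nothing in any analysis, including intention-to-treat. The document does not support that. Secondary outcomes are adjusted for baseline score, which does not cancel in this way. No covariate set is stated for intention-to-treat, and a comparison of randomised organisations does not need one for validity.

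A reader might also fear chance imbalance between arms. Level imbalance is already removed by the contrast. A covariate gap as large as 0.8 SD would be 9.3 to 3.4 standard errors: SE = √(2(1 + 28ρ)/348) = 0.086 to 0.232 for assumed covariate ICCs ρ of 0.01 to 0.3.

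Finally, the sample size section argues that ICCs are lower "when estimates are adjusted by participant baseline characteristics". That is one of several general reasons given there, and no figure changes.

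**Conclusion.** The point holds for the per-protocol primary analysis. For participants measured at both times, time-constant main-effect covariates cancel from the time-by-arm effect by algebra, without simulation assumptions, in linear and Poisson random-intercept models. The mitigation promised in the Outcomes section is therefore largely not delivered. The planned complete case analysis would show the same cancellation if it used this model.

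The size of the resulting bias cannot be derived from the protocol. It is the slope of change on the covariate times the covariate gap between recipients and controls, and neither is given. The illustrated 3.34 against a truth of 2 shows only that main effects leave such bias untouched, under assumed values and with all controls as comparators. The point does not extend to intention-to-treat, the secondary outcomes or the sample size.

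**What to change.** Amend Statistical methods {20a} in one of two ways, naming the choice in advance because the two rest on different assumptions in a non-randomised comparison:

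- keep the repeated-measures model and add the interaction of time with each genuine baseline covariate (age, gender, education, ethnicity); or
- model the 6-month count on arm, baseline count and these four covariates, with organisation as a random effect.

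In {20b}, take the kind and amount of MHFA experienced out of the adjustment set. It measures exposure to the intervention, and crossing it with time would absorb the treatment effect. It can be described separately.

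The cost is wording and a few more parameters, with 24 organisations; no new data are needed. The second option makes no use of people without a 6-month count unless they are imputed. Adding baseline wellbeing and help-seeking intentions, already in Table 1, is optional. Neither option deals with unmeasured confounding of change, and the Outcomes section should say so.

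### The primary effect is defined both as a 6-month mean difference and as an exponentiated time-by-arm interaction; one coefficient cannot be both, and only the first matches the sample size

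*Protocol article*

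**What the plan says.** Statistical methods for primary and secondary outcomes {20a} contains the following:

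- **First definition.** The analysis "will estimate the mean difference (with 95% confidence intervals) in the Actual Help-Seeking score at 6-month follow-up between the intervention (MHFA) and standard care groups".
- **Outcome and predictor.** "The dependent variable will be the count of help sources on the Actual Help-Seeking questionnaire". "The independent variable will be ‘time point"; a main effect of arm is neither listed nor excluded.
- **Second definition.** "The effect size of the intervention will be estimated as the exponentiated coefficient for the interaction term between time point (baseline versus 6-month follow-up", crossed with MHFA versus control.
- **Baseline.** "A random effect of participant will be included in the model to adjust for the repeated measures on participants", so the baseline count enters as one of the repeated outcomes. Other baseline characteristics are fixed effects, and the baseline AHSQ is not named among them. The paragraph on secondary outcomes adds: "All models will be adjusted for employing organisation and baseline score (where applicable".

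No distribution or link is given. Nothing says which of the two quantities is the result, or how one is obtained from the other.

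Sample size {14} works from a difference in means, "assuming that the mean in the control group is 1 and in the intervention group 3 with a common standard deviation of 8". The primary outcome text under Outcomes {12} restricts the primary analysis to people who receive MHFA. It acknowledges that this group is not a random part of those randomised and that selection and confounding may affect the result.

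**The concern.** The two definitions differ in two ways.

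- **Scale.** A mean difference is additive. An exponentiated coefficient has a natural meaning under a log link, where it is a ratio.
- **Contrast.** The first compares arms at 6 months. The second compares how the arms changed between baseline and 6 months.

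The reported effect, its interval and its relation to the powered difference therefore depend on which sentence the analyst follows. If this stays open until allocation is known, the choice can be made with the results in view.

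**Working it through.** **1. What the sample size tests.** Inputs from Sample size {14}: difference 3 − 1 = 2, SD 8, alpha 0.05, power 80%, attrition 15%, cluster size 29, ICC 0.01.

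- Two-sided, two-sample t-test with standardised difference 2/8 = 0.25: 252.13 per arm, so 253 per arm and 506 in total. This matches the stated figure. A one-sided test gives 396 (normal approximation) and does not match.
- Attrition: 506/0.85 = 595.3, so 596. Matches.
- Clustering: 1 + (29 − 1) × 0.01 = 1.28, and 596 × 1.28 = 762.88, so 763. Matches.

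The trial was therefore sized for a simple difference in 6-month means, with no baseline correlation.

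**2. What each definition returns.** The 6-month means are the planning values (MHFA 3, control 1). The protocol gives no baseline means, so those below are assumptions. The ratio is exp(interaction) under a log link, (MHFA 6-month/baseline) ÷ (control 6-month/baseline).

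| MHFA baseline | Control baseline | 6-month difference | exp(interaction) |
|---|---|---|---|
| 1 | 1 | 2 | (3/1)/(1/1) = 3.0 |
| 1.5 | 1 | 2 | (3/1.5)/(1/1) = 2.0 |
| 2 | 1 | 2 | (3/2)/(1/1) = 1.5 |
| 1 | 1.5 | 2 | (3/1)/(1/1.5) = 4.5 |

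The 6-month difference is the same in every row, while the ratio runs from 1.5 to 4.5. Nor does a ratio fix a difference: a ratio of 3 goes with a difference of 1, 2, 4 or 8 when the control mean is 0.5, 1, 2 or 4.

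If the model were linear, which is the plain reading of a mean difference, and its coefficient of 2 were exponentiated as the later sentence says, the result would be exp(2) = 7.39. That is neither a difference nor a ratio of means.

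**3. Precision, conditional on the model.** Suppose a main effect of arm is fitted and the scale is linear. The interaction is then a difference in change. Relative to the 6-month comparison, its variance is 2(1 − r), against 1 − r² with baseline adjustment, where r is the baseline to 6-month correlation. The documents do not give r, so a range is shown. Power = Φ(2/[8√(2v/253)] − 1.96), with v the relative variance and 253 per arm. At v = 1 this gives 80%.

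| r (assumed) | v, interaction | v, adjusted | Power, interaction | Power, adjusted |
|---|---|---|---|---|
| 0.3 | 1.40 | 0.91 | 66% | 84% |
| 0.5 | 1.00 | 0.75 | 80% | 90% |
| 0.7 | 0.60 | 0.51 | 95% | 98% |

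Without a main effect of arm, the interaction is the constrained-baseline estimator and loses nothing. In a simulation at r = 0.5 with 253 per arm, its standard error was 0.624, against 0.718 with the main effect and 0.718 for follow-up alone.

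**The case against.** **The scales can be reconciled.** A log-link model can yield both a ratio and, by standardisation, a difference in means. With equal baselines the interaction ratio of 3 is simply the ratio of 6-month means, and no effect on one scale is no effect on the other. A count outcome with an exponentiated coefficient also points to a log link, which makes 7.39 an unlikely result in practice. All of this stands, so a reader who infers that one model cannot supply both quantities goes too far. It remains true that one coefficient cannot be both, that the protocol does not say which is primary, and that equal baselines cannot be taken for granted in this population.

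**Distribution and link belong in the SAP.** Agreed; their absence is not the point. Two conflicting definitions of the primary effect in one paragraph are a contradiction, not an omitted detail.

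**A reader might infer that the interaction wastes the baseline and costs planned power.** The documents do not support this. It needs a main effect of arm, which the text does not list. The baseline count does enter, as a repeated outcome. The variance formulas are linear-scale and ignore clustering, so they do not carry over directly to a count model. The 80% starting point belongs to the full planned sample, not to the per-protocol subsample. Above r = 0.5 the interaction is more precise than follow-up alone.

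**A reader might also infer that a common baseline mean can be imposed because allocation follows baseline.** That holds for the intention-to-treat analysis of all respondents. It does not hold for the per-protocol primary analysis, where randomisation does not guarantee equal baselines and forcing equality could add bias.

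**Conclusion.** The point holds as a contradiction in the stated primary analysis. On the plan's own 6-month means, with both baselines assumed to be 1, the two sentences give 2 and 3, or 7.39 if a linear coefficient is exponentiated literally. With unequal baselines the two measures separate further, and the per-protocol population makes that a practical concern. Only the 6-month mean difference agrees with the sample size.

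The efficiency argument is secondary. It depends on an unstated model term and an assumed r, and does not show that the plan as written loses power. The choice between change from baseline and baseline adjustment also affects what is estimated in a self-selected group, so it is not only a matter of precision.

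**What to change.** 1. Name one primary effect measure: the between-arm difference in mean number of help sources at 6 months, with its 95% CI, obtained by standardisation from a log-link count mixed model. Report the 6-month rate ratio as a supporting result.
2. Remove the exponentiated interaction as the definition of the effect.
3. State how the baseline AHSQ enters. Adjusting the 6-month count for the baseline count is the simple option and matches the approach for the secondary outcomes. If the repeated-measures form is kept, state whether a main effect of arm is fitted, because that changes what the interaction estimates.
4. Do not rest a common-baseline constraint on randomisation in the per-protocol analysis; keep it, if wanted, for the intention-to-treat analysis.

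The cost is wording in the protocol and SAP, settled before unblinding. No new data are needed, since the AHSQ is already collected at baseline, and this point does not alter the sample size basis. The downside is that the confidence interval on the difference scale needs the delta method or a bootstrap.
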